#### AI Model Development (OMNIdiasense)

The AI tool will be codeveloped by the MoH digital-health team and computer scientists from Sultan Qaboos University. The development pipeline comprises 7 steps, expanded below to address missing data, class imbalance, overfitting, feature selection, calibration, fairness, and external validation.

Data preparation: integration and cleaning of deidentified data from substudies 1 and 2 (demographic, clinical, laboratory, anthropometric, psychosocial, and behavioral).Feature engineering: selection of candidate predictors informed by substudy 2 effect sizes and clinical face validity.Model selection and training: comparison of supervised classifiers (logistic regression, gradient-boosted trees, support vector machines, and a small feed-forward neural network) using stratified cross-validation; evaluation by area under the receiver operating characteristic curve, sensitivity, specificity, calibration, and net reclassification improvement.Behavioral pattern recognition: unsupervised clustering of lifestyle and dietary data to derive interpretable phenotypes used for personalized recommendations.Initial testing: internal validation on a held-out 20% partition.Optimization: iterative refinement on the basis of clinician and family feedback.Deployment: secure web-based interface integrated into the diabetes clinic workflow with role-based access and audit logging.

#### Handling of Missing Data, Class Imbalance, Overfitting, and Feature Selection

Missingness will be quantified by variable and pattern. Variables with >40% missingness will be excluded unless they carry strong prior clinical value, in which case they will be retained with an explicit missing indicator. Item-level missing data on validated scales will be imputed using each scale’s published rules; remaining missingness will be addressed by multiple imputation by chained equations (m=20) under a missing-at-random assumption, with a tipping-point sensitivity analysis to test robustness against a missing-not-at-random scenario.

Class imbalance between optimizers and subusers will be addressed at 2 levels: stratified sampling during cross-validation to preserve outcome proportions in every fold, and class-weighted loss functions (inverse-frequency weights) for the gradient-boosted, SVM, and neural-network classifiers. Synthetic minority oversampling will be evaluated as a sensitivity analysis only and not as the primary approach, to avoid optimistic generalization.

Overfitting will be controlled through nested cross-validation (outer 5-fold for performance estimation, inner 5-fold for hyperparameter tuning), L1/L2 regularization for linear models, early stopping and shrinkage for boosted trees, and dropout and weight decay for the neural network. The full train-test partition (80/20) will be temporally separated where possible (children enrolled later become the held-out set) to give a more realistic estimate of prospective performance.

Feature selection will use a stability-selection wrapper around L1-penalised logistic regression with 100 subsampled fits; features selected in ≥60% of subsamples will be retained, in addition to a clinically prespecified core set (age, sex, diabetes duration, baseline HbA_1c_, insulin modality, governorate, BenCGM, BurCGM, SEDM, and PAID-Peds). The final model will be sparse and interpretable; Shapley additive explanations (SHAP) values will be reported to support clinical interpretation of individual predictions.

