**Objective:**

This multiphase translational research project aims to (1) characterize the population of Omani children with T1DM; (2) identify demographic, psychosocial, dietary, and physical activity correlates of optimal CGM use; (3) develop, train, and validate an AI-assisted behavioral predictive tool “OMNIdiasense” to forecast CGM adherence prior to device dispensing; and (4) pilot test the OMNIdiasense tool.

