**Figure 1 figure1:**
[figure not shown]
Multiphase study flow of the OMNIdiasense project. AUROC: area under the receiver operating characteristic curve; BenCGM: Benefits of Continuous Glucose Monitoring Scale; BP: blood pressure; BurCGM: Burden of Continuous Glucose Monitoring Scale; CGM: continuous glucose monitoring; HbA1c: hemoglobin A1c; HIS: health information system; LFT: liver function test; MoH: Ministry of Health; NN: neural network; PAID: Problem Areas in Diabetes; PAQ-A: Physical Activity Questionnaire for Adolescents; RFT: renal function test; RSQ: Response to Stress Questionnaire;
SEDM: Self-Efficacy for Diabetes Management Scale; SQU: Sultan Qaboos University; SVM: support vector machine; T1DM: type 1 diabetes mellitus; TRIPOD+AI: Transparent Reporting of a Multivariable Prediction Model for Individual Prognosis or Diagnosis + Artificial Intelligence.

**Table 1 table1:** Description of the substudies by design, outcomes, and how each informs the next.

Substudy and aim	Design	Primary outputs/outcomes	How it informs the next phase
Substudy 1: characterize population	Retrospective cohort (Al Shifa records, n~1500)	Population characterization; pre/post HbA_1c_^a^, anthropometrics, BP^b^, lipids, RFT^c^, LFT^d^; sensor-wear days per week; baseline adherence prevalence	Provides the deidentified structured dataset (clinical + adherence label) used as the supervised-learning input for OMNIdiasense; defines candidate clinical predictors.
Substudy 2: identify correlates	Cross-sectional mixed methods (n=240 face-to-face interviews + qualitative open-ended responses)	Quantitative effect sizes for BenCGM^e^, BurCGM^f^, RSQ^g^, SEDM^h^, PAID-Peds^i^, PAQ-A^j^, and dietary screener on optimizer vs subuser status; qualitative themes on barriers and facilitators	Provides the psychosocial and behavioral feature set, the qualitative themes that inform MI content, and the effect sizes used to prioritize features for the AI model.
Substudy 3: AI tool development (7-step pipeline with validation hierarchy)	Prediction model development on combined substudy 1 + 2 dataset	OMNIdiasense risk score (probability of subuser status), with discrimination, calibration, and fairness metrics	The validated model becomes the assessment tool tested in the 2 evaluation arms below.

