#### Sample Size

Assuming an optimizer prevalence of approximately 50% [25] and aiming to detect medium-effect-size predictors in a multivariable logistic model with up to 8 predictors, a minimum of 240 participants will provide sufficient statistical power (≥10 events per variable). Recruitment will be stratified across the 11 governorates proportional to CGM dispensations.

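### Four core psychosocial predictors are measured only in the interviewed children, after CGM use is established; the protocol does not say which children train the model that contains them

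*Protocol article*

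**What the plan says.** Table 1 describes substudy 1 as "Retrospective cohort (Al Shifa records, n~1500") and gives it the role of supplying clinical variables and the adherence label as the supervised-learning input. The substudy 1 extraction list (Data Collection) contains no psychosocial scale.

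BenCGM, BurCGM, SEDM and PAID-Peds appear only in the substudy 2 interview (Measurements), which Table 1 gives as "Cross-sectional mixed methods (n=240 face-to-face interviews + qualitative open-ended responses"). The interviewees are aged 10-18 and sampled from substudy 1, so they add no new children to the combined data.

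Table 1 gives the design of the AI step as "Prediction model development on combined substudy 1 + 2 dataset", and step 1 of the AI Model Development section integrates the two sources.

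The section on missing data and feature selection contains two rules that meet here:

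- On missingness: "Variables with >40% missingness will be excluded unless they carry strong prior clinical value". A variable kept under the exception carries a missing indicator, and remaining gaps go to chained-equation imputation (m=20) under missing at random.
- On features: a core set fixed on clinical grounds is retained whatever the stability selection shows. It has 10 members and ends with "governorate, BenCGM, BurCGM, SEDM, and PAID-Peds".

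The stated purpose of the tool (Abstract, Objective) is "to forecast CGM adherence prior to device dispensing".

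**The concern.** The protocol never says which children train and test the model that contains the four scales, and the two available readings lead to different analyses.

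If the training set is the whole substudy 1 cohort, the scales are absent for most children because those children were never interviewed. The rule for heavily missing variables is then applied to a block that is missing by design. Retention with an indicator adds a flag that mainly separates interviewed from non-interviewed children. At deployment every assessed child would presumably complete the scales, so the flag would be constant there and its training coefficient would have no counterpart in use. Most scale values in training would come from the imputation model.

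If the training set is the linked interview sample, that difficulty disappears, but the model is then developed on about 240 children, which should be stated.

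Timing is a separate problem under both readings. The scales are collected from children who have had CGM for many months and are already classed as optimizers or subusers, including some who stopped. Perceived benefit and burden at that point may result from use as much as predict it. The tool is meant to score children who have not yet had a sensor.

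**Working it through.** **Inputs**

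- Substudy 1 records: about 1500 (Table 1).
- Interviews: 240 (Table 1), a minimum (Substudy 2, Sample Size), nested in substudy 1.
- Missingness limit: 40%.
- Assumed optimizer prevalence: about 50% (Substudy 2, Sample Size), so about 50% subusers.
- Training share: 80%.
- Core set: 10 variables; 11 governorates.

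The protocol states no missingness figure for the scales, so there is none to reproduce.

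**Reading A: all substudy 1 records enter training**

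Missing fraction = 1 − 240/N.

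- N = 1500: 1 − 240/1500 = 84%, which is 1260 rows without scales, or 5.25 for each row with them.
- The number aged 10-18 is not given. Assumed values of N: 1200 gives 80%, 1000 gives 76%, 750 gives 68%, 600 gives 60%, 500 gives 52%, 400 gives 40%.
- Break-even: 240/(1 − 0.40) = 400. Any training cohort above 400 exceeds the limit. With all 1500 in training, 0.60 × 1500 = 900 interviews would be needed to meet it.

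**Reading B: only the linked 240 enter training**

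- Scales missing by design: 0%.
- Training part: 0.8 × 240 = 192 children; held out: 48.
- Subusers in training: 192 × 0.5 = 96.
- Per core variable: 96/10 = 9.6.
- If governorate is dummy-coded (10 indicators) and the other nine variables take one parameter each: 19 parameters, 96/19 = 5.05 per parameter.
- Features added by stability selection come on top.

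For comparison, the substudy 2 regression with up to 8 predictors gives 240 × 0.5/8 = 15 events per variable, so its own statement, "a minimum of 240 participants will provide sufficient statistical power (≥10 events per variable"), holds as far as the ratio goes.

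**Timing, both readings**

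- Substudy 1 children received CGM from July 2024 to February 2025 (Substudy 1, Design and Population).
- Substudy 2 recruitment is planned to begin in June 2026 (Results).
- From the end of February 2025 to the start of June 2026 is 15 months, so scales are completed at least 15 months after a child first received CGM.
- RCT children must not yet have received CGM (Inclusion and Exclusion Criteria).
- The 20% held-out part comes from the same children with the same timing, even when the split is by enrolment date.

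**The case against.** The strongest reply is that joining the clinical record to the interview for the 240 is a natural meaning of combining the two substudies. Diabetes duration is to be imported from substudy 1 into the interview data, and a full analysis plan exists that may name the training rows. That stands as far as it goes: 84% is conditional, not a fact about the plan. But Table 1 also calls the substudy 1 dataset the supervised-learning input, so the wider reading is equally open, and the missingness rule as written would operate under it.

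Several stronger inferences are tempting and not supported:

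- *The 40% rule removes the scales.* It has an exception for clinically important variables, and the same section names these four in the core set. The live branch is retention with an indicator and imputation.
- *Children under 10 are in the training data.* Substudy 1 states no age limit, but the tool and the fairness bands are for ages 10-18, and nothing says younger children enter training.
- *Performance will be quoted as if based on 1500 children, or subusers will refuse interview more often.* The protocol says neither. It plans to describe missingness by variable and pattern and to run a tipping-point analysis.
- *The model falls to half the plan's own standard of 10 events.* That standard sizes the substudy 2 regression and counts variables; on that count the core set gives 9.6. The figure of about 5 needs dummy coding that the protocol does not specify. The planned penalties, early stopping and nested cross-validation also soften it.

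On timing, the External Validation section plans a temporal cohort and an external replication, and the score may not affect CGM access. These limit the harm. The section does not say, however, that the temporal cohort completes the scales before CGM start, so the point remains open.

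**Conclusion.** The concern holds in a conditional form. The protocol puts four interview-only scales into a model developed on combined data without saying which children train it. If the whole cohort is used, the scales are absent by design for about 84% of rows (assuming all 1500 records and exactly 240 interviews), and for more than 40% in any cohort above 400. The planned indicator would then largely mark interview participation. If only the interviewed children are used, the development size is about 240, with about 96 subusers in the training part: 9.6 per core variable, or about 5 per parameter under dummy-coded governorate, before further features and subject to penalization.

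The timing point depends on neither reading. Internal performance, including the held-out AUROC, will describe how well the scales separate children whose pattern of use is already set. It cannot by itself support a claim of prediction before dispensing.

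This should be corrected before modelling starts; feature engineering is scheduled for the third quarter of 2026.

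**What to change.** 1. State that the model containing the four scales is trained and tested only on interviewed children aged 10-18, and give that number as its development size.
2. Use substudy 1 children aged 10-18 for a separate clinical-only model.
3. Do not impute whole scales, or use a missing indicator, for children who were never interviewed. Keep the 40% rule and imputation for gaps among children who were meant to be measured.
4. Consider a coarser or penalized coding of governorate in the model, while keeping the fairness audit by governorate.
5. Report substudy 2 performance as concurrent classification.
6. Base any pre-dispensing claim on the planned temporal validation cohort, and specify that its scales are completed before CGM start. RCT controls can be supporting data only: there are 25 of them, and the 25 intervention children receive support meant to change the predicted outcome.

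The cost is mainly wording in the protocol and analysis plan, plus fixing when the temporal cohort completes the scales and, if RCT controls are used in support, giving them the scales at baseline. The downside is that the stated development size of the full model falls from about 1500 to about 240.

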#### Calibration

Discrimination alone is insufficient when a model is used to triage clinical support. Calibration will be assessed using calibration plots, the Brier score, calibration-in-the-large, and calibration slope. If the raw model is miscalibrated, isotonic regression or Platt scaling will be applied to the inner cross-validation folds and reevaluated on the outer fold. Decision-curve analysis across plausible threshold probabilities will accompany the calibration report.

#### Fairness Across Sex, Age, and Governorate

Fairness will be evaluated as a primary model-quality dimension, not as an afterthought. For each protected attribute (sex, age band 10-13 years vs 14-18 years, and governorate), we will report subgroup-specific area under the curve, sensitivity, specificity, calibration slope, and false-negative rate (the most consequential error, since a false negative could deny behavioral support to a child who needs it). Equality of opportunity and predictive parity will be reported. If a clinically meaningful disparity is detected (absolute difference in false-negative rate >10 percentage points), we will apply group-specific threshold adjustment and reevaluate before deployment.

#### External Validation

Internal validation alone is insufficient before clinical use. The validation plan therefore includes three layers: (1) internal validation on the held-out 20% partition, (2) temporal validation on a prospectively collected cohort enrolled at least 3 months after model lock, and (3) a preplanned external multisite replication in 2 Gulf neighboring sites (institutions to be confirmed at the start of the pilot phase) using the same data-collection forms and the same outcome definitions. Until external validation is satisfactory, OMNIdiasense outputs will be presented to clinicians as decision support only and will not influence CGM allocation (see the Ethical Considerations section).

#### Reporting Standard

Reporting of the AI development will follow the TRIPOD+AI (Transparent Reporting of a Multivariable Prediction Model for Individual Prognosis or Diagnosis + Artificial Intelligence) guideline [44,45], which provides a 27-item checklist for prediction-model studies that use traditional regression or AI/machine learning methods. The TRIPOD+AI checklist will be uploaded with the results paper.

#### Personalization and Feedback Mechanism

OMNIdiasense will generate a per-patient adherence-risk score with personalized, MI-aligned recommendations covering meal timing, physical activity, stress management, and parental engagement. The system will be piloted in Muscat for 6 months prior to wider testing.

#### Sample Size

The pilot RCT sample size was based on the prevalence of optimal CGM use of approximately 50% [25] and a moderate effect (odds ratio 0.53) reported for adolescent CGM use. Using G*Power 3.1 (Heinrich Heine University Düsseldorf), at least 25 participants per arm are required to achieve 80% power at α=.05. The single-arm component (n=100) is powered for paired-sample within-person change in adherence and HbA_1c_.

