Substudy 3: quasi-experimental single-arm pilot	Quasi-experimental, n=100 existing subusers	Within-person change in adherence and HbA_1c_ after OMNIdiasense-guided MI sessions	Feasibility, acceptability, and effect-size estimates for a future definitive trial.
Substudy 3: pilot RCT^k^ with appropriate reporting standards	Parallel 1:1, n=50 newly diagnosed (25 intervention, 25 control)	Between-group difference in CGM^l^ adherence at 12 months; secondary clinical, behavioral, and satisfaction outcomes	Generates the effect-size, recruitment, retention, and fidelity estimates required for a definitive multicenter trial.

^a^HbA_1c_: hemoglobin A_1c_.

^b^BP: blood pressure.

^c^RFT: renal function test.

^d^LFT: liver function test.

^e^BenCGM: Benefits of Continuous Glucose Monitoring Scale.

^f^BurCGM: Burden of Continuous Glucose Monitoring Scale.

^g^RSQ: Response to Stress Questionnaire.

^h^SEDM: Self-Efficacy for Diabetes Management Scale.

^i^PAID-Peds: Problem Areas in Diabetes-Pediatric version.

^j^PAQ-A: Physical Activity Questionnaire for Adolescents.

^k^RCT: randomized controlled trial.

^l^CGM: continuous glucose monitoring.

CGM distribution in Oman commenced in May 2024 following extensive capacity-building of diabetes clinic staff in 30 health facilities across all governorates. By February 2025, approximately 1500 children with T1DM had received CGMs, recorded centrally in the national Al Shifa health information system.

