#### Outcomes

The primary outcome is the between-group difference in CGM adherence, defined as mean days per week of sensor wear over the 12-month follow-up. The CGM adherence outcome will be measured from pharmacy dispensing records, self-report, and clinical records. Differences between device types will be recorded, and significant findings across different devices will be analyzed.

Key secondary outcomes are change in HbA_1c_, time in range, anthropometric measures (weight and BMI), blood pressure, lipid panel, RFT, LFT, drug/treatment changes, OMNIdiasense risk score change, barriers and facilitators of CGM use, and patient satisfaction (Multimedia Appendix 9). Table 2 shows the full schedule of assessments.

**Table 2 table2:** Schedule of assessments in substudy 3.

Variable		Tool/source	Baseline	3 months	6 months	12 months

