#### Randomization and Blinding

In the RCT component, computer-generated 1:1 simple randomization will be performed centrally by an independent statistician. Allocation concealment will use sequentially numbered, opaque, sealed envelopes opened only after enrollment confirmation. Outcome assessors and the data analyst will be blinded to allocation; participants and intervention deliverers will not be blinded owing to the nature of the intervention.

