## Discussion

### Anticipated Principal Findings

We anticipate 3 principal findings. First, substudy 1 is expected to show that pediatric CGM uptake in Oman is high in the first 6 months of dispensing, but that a clinically important minority becomes subusers by month 3, with measurable variation across governorates. Second, substudy 2 is expected to confirm prior international findings that perceived benefit and burden of CGM, self-efficacy, and diabetes distress are the strongest psychosocial correlates of optimizer status, with additional Omani-specific contributors emerging from the open-ended responses. Third, substudy 3 is expected to show that OMNIdiasense, used as a decision-support adjunct followed by MI-guided behavioral sessions, is feasible to deliver, acceptable to families and clinicians, and produces a clinically meaningful between-group difference in adherence at 12 months that can power a future definitive trial.

These anticipated findings are framed as testable hypotheses, not foregone conclusions, and all statements throughout the abstract, manuscript, and conclusion have been rechecked to ensure that the strength of language matches the strength of inference that the proposed methodology can support.

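### The pilot RCT's 25 per arm does not give 80% power for 50% prevalence and an odds ratio of 0.53: power is about 14–23%, and about 160 per arm would be needed

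*Protocol article*

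**What the plan says.** The Sample Size section of substudy 3 bases the pilot RCT on about 50% optimal CGM use and "a moderate effect (odds ratio 0.53) reported for adolescent CGM use". It names G*Power 3.1 as the software and concludes that "at least 25 participants per arm are required to achieve 80% power at α=.05". It does not state sidedness, test family, SD, within-child correlation or a dropout allowance.

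Table 1 gives the design as "Parallel 1:1, n=50 newly diagnosed (25 intervention, 25 control"), so the number enrolled equals the number said to be required.

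The Outcomes section makes the primary outcome continuous: "The primary outcome is the between-group difference in CGM adherence, defined as mean days per week of sensor wear over the 12-month follow-up". Table 2 also lists the binary optimizer/subuser classification under the primary outcome. The Data Analysis section of substudy 3 names t tests, chi-square tests and mixed models for the between-group comparison.

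Among its anticipated findings, the Discussion says that the tool with MI support "produces a clinically meaningful between-group difference in adherence at 12 months that can power a future definitive trial".

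**The concern.** The article prints the inputs, the software and the answer, so the answer can be checked. A 15-point difference between two proportions near 50% needs well over a hundred participants per arm, and 25 is too few by a factor of more than six.

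Two further mismatches lie behind the number:

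- The inputs are binary, while the Outcomes section defines a continuous primary outcome.
- The odds ratio is described as one reported for adolescent CGM use. It is not described as the effect of a risk score plus motivational interviewing.

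The consequences run both ways. If readers believe the trial has 80% power, they will take a null result as evidence against the intervention, although the trial had little chance of detecting the planned effect. The data monitoring committee may also recommend stopping for futility, and a futility judgement made against a false power figure would be misinformed. Conversely, a result that does reach significance must come from an observed effect well above the planned one. Carrying that estimate into the definitive trial, as the Discussion envisages, would make the next trial too small.

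**Working it through.** **Inputs.** From the Sample Size section of substudy 3: control proportion p1 = 0.50, odds ratio 0.53, alpha 0.05, 80% power, 25 per arm. From Table 1 and Randomization and Blinding: 1:1 allocation. Sidedness is not stated. Two-sided is assumed, and one-sided is shown as well.

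**Step 1: what the odds ratio means.** At p1 = 0.50 the odds are 1, so p2 = 0.53/(1 + 0.53) = 0.346. Inverted, p2 = 1/(1 + 0.53) = 0.654. Either way the difference is 0.154.

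**Step 2: trying to reproduce 25 per arm.** With mean proportion p̄ = (0.500 + 0.346)/2 = 0.423,

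n = [1.96·√(2p̄(1−p̄)) + 0.842·√(p1(1−p1) + p2(1−p2))]² / (p1−p2)²

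= [1.96·√0.488 + 0.842·√(0.250 + 0.226)]² / 0.1536²

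= (1.369 + 0.581)² / 0.0236 = 161.2, which rounds up to **162 per arm**.

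Other versions of the calculation agree:

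| Method | Two-sided, per arm | One-sided, per arm |
|---|---|---|
| Pooled normal | 162 | 127 |
| Unpooled normal | 159 | 125 |
| Arcsine | 162 | 127 |
| Log odds ratio | 164 | 130 |
| Same odds ratio, rates centred on 50% | 158 | 124 |
| Continuity-corrected | 175 | 140 |
| t test, odds ratio converted to d = 0.35 | 130 | 102 |

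The conversion in the last row is d = |ln 0.53|·√3/π = 0.635 × 0.551 = 0.35. It assumes a logistic latent scale, because the article gives no SD or expected difference for days per week.

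**Step 3: power at 25 per arm.**

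| Test | Two-sided | One-sided |
|---|---|---|
| Pooled normal approximation | 19.2% | 29.0% |
| Chi-square, uncorrected, full enumeration | 22.3% | 31.8% |
| Fisher's exact, full enumeration | 14.5% | 22.2% |
| t test, d = 0.35 | 22.8% | 33.6% |

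**Step 4: what 25 per arm can detect.** Two-sided with 80% power, it detects 50% versus about 86% (odds ratio 0.86/0.14, about 6.2), or d of about 0.81. Neither is stated, and neither fits the article's word for the effect, moderate.

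**Step 5: what would give about 25.** Figures near 25 appear only with inputs that the article does not state:

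- d = 0.8 in a two-sample t test gives 26 per arm.
- 0.53 misread as a standardized effect in a one-sided paired test gives 24.
- d = 0.35 averaged over four completely uncorrelated measurements, one-sided, gives 26. With a correlation of 0.5 between measurements this becomes 64 one-sided and 81 two-sided.
- 0.53 misread as d in the actual two-arm comparison still needs 57 per arm two-sided or 45 one-sided.

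**Step 6: precision and exaggeration.** The 95% CI half-width is 1.96·√((0.250 + 0.226)/25) = 0.27, or ±27 percentage points, on the proportion scale. On the standardized scale it is 1.96·√(2/25) = 0.55 SD. To reach p < 0.05 on a t test, the observed d must be about 0.57, which is 0.57/0.35 = 1.6 times the effect assumed.

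**The case against.** The best defence is that this is a pilot. Table 1 says it will provide effect-size, recruitment, retention and fidelity estimates. The limitations concede that the sample is modest and that pilot effects need confirmation in a definitive trial. The Discussion presents its expectations as hypotheses to be tested, and reporting is to follow the CONSORT extension for pilot trials. No go/no-go rule is tied to significance. On those terms 50 children is a reasonable number. This supports the size, but none of it withdraws the 80% power statement, which is explicit and wrong.

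Some narrower points do stand:

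- The 14% is for Fisher's exact test, which is not a planned test. For the two simple tests that are named, power is 22–23%.
- Power on the days-per-week scale cannot be derived from the article's own inputs. The 0.35 SD is a conversion, and days per week is bounded at 7 and probably skewed. Averaging repeated measurements could improve precision, by an amount that depends on a correlation the article does not give. On that scale the 80% claim is strictly unsupported, and it is false under the conversion used here.
- Table 2 gives the binary outcome some standing as primary, so a binary sample-size basis is not without textual support. The headline figures are on that binary scale.
- That a null result would be misread is a judgement about readers, not something the article says.

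**Conclusion.** The point holds. On the binary scale that the calculation uses, 25 per arm gives about 14–23% power two-sided, not 80%. About 162 per arm would be needed, more than six times the stated number. This rests on the article's 50%, 0.53, 0.05 and 1:1, plus two-sided testing. One-sided testing raises power to at most about 34% and still needs more than 100 per arm. On the days-per-week scale, under the stated conversion, power is 23% and 130 per arm are needed. No test or sidedness applied to the stated inputs in the two-arm comparison brings the requirement near 25. Because the statement concerns the primary comparison of the randomized component, it must be corrected.

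**What to change.** - Delete the 80% power claim from the Sample Size section of substudy 3.
- State that 50 children is a feasibility size. Give its precision (about ±27 percentage points on the optimizer proportion, ±0.55 SD on days per week) and, if the odds ratio of 0.53 is kept, the power at that effect (about 14–23%).
- Say that the between-group difference will be reported as an estimate with its 95% CI, without a conclusion based on significance.
- Reword the Discussion so that the definitive trial is sized on a minimum important difference together with the pilot's SD and retention, not on the pilot's point estimate.

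The cost is wording only. The stated power becomes much less favourable, and no extra participants are needed. The article plans substudy 3 recruitment for the fourth quarter of 2026, so its own timeline leaves room to correct this before enrolment.
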